# Design paper: The CapOpus trial: A randomized, parallel-group, observer-blinded clinical trial of specialized addiction treatment versus treatment as usual for young patients with cannabis abuse and psychosis

**DOI:** 10.1186/1745-6215-9-42

**Published:** 2008-07-11

## Abstract

**Background:**

A number of studies indicate a link between cannabis-use and psychosis as well as more severe psychosis in those with existing psychotic disorders. There is currently insufficient evidence to decide the optimal way to treat cannabis abuse among patients with psychosis.

**Objectives:**

The major objective for the CapOpus trial is to evaluate the additional effect on cannabis abuse of a specialized addiction treatment program adding group treatment and motivational interviewing to treatment as usual.

**Design:**

The trial is designed as a randomized, parallel-group, observer-blinded clinical trial. Patients are primarily recruited through early-psychosis detection teams, community mental health centers, and assertive community treatment teams. Patients are randomized to one of two treatment arms, both lasting six months: 1) specialized addiction treatment plus treatment as usual or 2) treatment as usual. The specialized addiction treatment is manualized and consists of both individual and group-based motivational interviewing and cognitive behavioral therapy, and incorporates both the family and the case manager of the patient.

The primary outcome measure will be changes in amount of cannabis consumption over time. Other outcome measures will be psychosis symptoms, cognitive functioning, quality of life, social functioning, and cost-benefit analyses.

**Trial registration:**

ClinicalTrials.gov NCT00484302.

## Background

A recent meta-analysis of eleven longitudinal studies concluded that cannabis use is associated with increased risk of lasting psychotic conditions later in life [1]. Assuming causality, as much as 800 annual cases of schizophrenia are preventable in the UK if exposure to cannabis was eliminated [2]. Several studies have shown that use of cannabis increases the risk of developing schizophrenia-like symptoms, especially in young men disposed to developing psychosis [3-10]. Furthermore, use of cannabis among patients with psychosis can maintain and worsen the psychotic symptoms [11-15], and comorbid schizophrenia and substance abuse is associated with lack of compliance to treatment and with more rehospitalizations [15-20]. This indicates both that effective interventions to limit cannabis use in persons with psychosis are needed, and that getting patients to follow such interventions may be difficult.

A randomized trial showed that the combination of cognitive behavioral therapy, motivational interviewing [see [21]], and family involvement had a significant positive effect on level of functioning, psychotic symptoms, and duration of periods of cannabis-abstinence, compared with regular treatment [22]. This finding has been supported by two reviews, concluding that positive evidence exists for integrated treatment with motivational interviews, cognitive behavioral therapy (individual or group-based), and a harm-reduction approach [23,24]. Group-based treatments are arguably less expensive, and in a literature review, Weiss et al. concluded that specialized group therapy could reinforce the effect of an existing treatment [25]. However, there is currently insufficient evidence to show that group-based interventions for cannabis use are superior to individual treatment [26,27]. Similarly, authors of a recent Cochrane review concluded that insufficient evidence exists to show that any psychosocial treatment method for comorbid schizophrenia and substance abuse is superior to others [28].

### Objectives of the CapOpus trial

We plan to undertake a trial in which combined group-based and individual treatment, incorporating motivational interviewing, psycho-education, cognitive behavioral therapy, and social skills training in addition to treatment as usual, is compared with treatment as usual. The primary outcome will be change in number of days abstinent from cannabis within the preceding 30-day period as measured with the Time-Line Follow Back (TLFB) instrument [29,30].

## Methods

The trial is designed as a two-armed, parallel-group, observer-blinded randomized clinical superiority trial (Figure 1). Patients will receive either specialized CapOpus treatment or treatment as usual, as described below.

**Figure 1 F1:**
[figure not shown]
**Flowchart of the CapOpus trial.** See text for further information.

### CapOpus intervention – the experimental intervention

The contents of the CapOpus intervention are briefly schematized in figure 2. An important part of the CapOpus treatment is to help the patient understand the mechanisms that complicate cessation of cannabis use. The overall target is harm reduction, i.e. that harm from cannabis consumption is thought to be alleviated even if consumption is not terminated, only reduced. This is a method that has proved effective in several studies [23,24]. The CapOpus intervention consists of one month of individual treatment, followed by a three-month group treatment in combination with individual treatment, and followed by two months of individual treatment. The contents of each of these three stages will be described in detail below.

**Figure 2 F2:**
[figure not shown]
Schematic timeline of the CapOpus intervention.

Upon inclusion, the patient's case manager at the referring institution will be offered education and supervision by one of the addiction consultants employed in the CapOpus trial.

During the first month, one of the addiction consultants will be in contact with each patient once or twice a week. A meeting will be held with the patient's family, and there will be contact with the case manager every two weeks. During the three months of group intervention, one of the addiction consultants will have weekly individual contacts with the patient and two meetings with the family. In addition, the patient will follow a weekly group intervention and have consultative contacts with the case manager every two weeks. During the two months following the group intervention, the addiction consultants will be in weekly contact with the patient and the family will be invited to a meeting. The addiction consultants will contact the patient's case manager every three weeks.

For the purpose of enhancing alliance and motivation, the treatment will start with motivational interviewing with the patient being aided in analyzing advantages and drawbacks of continued use of cannabis [21,31]. There is good evidence for the efficacy of motivational interviews in short-term treatment [32,33]. The patient will formulate individual goals for the treatment and be offered the group intervention. The groups will consist of six to eight patients, with the addiction consultants as trainers. Each group will run for three months with weekly sessions lasting 1 1/2 hour. The intervention methods will gradually shift from motivational interviewing to cognitive behavioral therapy as the patients become more motivated to change their cannabis use. There will be emphasis on analyzing advantages and disadvantages of continued use, instructions in coping skills in relation to craving and situations that usually trigger cannabis use, and in developing personal strategies for avoiding or handling these situations.

The group intervention will be followed by two months during which weekly meetings with the patient continue. The addiction consultants offer consultative assistance to the patient's case manager, as well as meeting the patient's family. The purpose is to mediate methods of the intervention to the network surrounding the patient in order to prolong beneficial effects.

To increase adherence to treatment, positive reinforcement will be applied through contingency management in the form of complimentary food and social experiences, which may enhance outcomes of cognitive behavioral therapy or motivational enhancement [34]. Contingency management in the CapOpus trial will have no connection to whether or not the use of cannabis is decreased.

The experimental CapOpus intervention is offered in addition to treatment as usual. The interventions offered to the patients will be registered so that it will be possible to estimate if the two intervention groups receive different forms of treatment as usual.

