### Sample size and power calculation

A 2008 Cochrane review of psychosocial interventions for people with both severe mental illness and substance misuse [28] identified five papers with results from studies using a combination of motivational interviewing and cognitive behavioral therapy.[22,64-67] However, only one of these contains information about reduction of days with cannabis abuse, but presents only the median, not the mean, and the range, not the standard deviation.[22] However, 6 months after start of treatment, this particular paper reported that those receiving integrated care had, as median, 20.62 percent of days abstinent from all substances, compared to 1.10 in the routine care group, i.e. a difference of 19.5. Extrapolating this to our study, with a TLFB-period of 30 days, corresponds to 5.85 days. Truncating this to a more conservative 5 days, and assuming a standard deviation also of 5 days, it becomes possible to calculate sample size for an independent samples t-test; with an α-level of 0.05 and a power of 0.90, the required number of patients in each intervention can be calculated to be 22. Due to attrition, more patients will be required. Results from the OPUS trial, which may be comparable to our study in terms of participant profiles, showed that high attrition may be expected among substance-using people with schizophrenia [38]. We obtained data about one-year dropout from the OPUS trial among people with substance misuse, and found that among those receiving the control treatment, the dropout-rate was 37%. Generalizing this to our study, regardless of intervention allocation, at least 35 patients will be required in each of the two intervention groups. However, we aim to include between 60 and 70 patients in each group, as this would enable us to stratify the analyses. With 60 or 70 patients, it should also be possible to measure even smaller differences in secondary outcomes.

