### Statistics

The main null-hypothesis to be tested is that there is no difference between the two treatment arms with regard to decrease in cannabis use. All randomized patients will be analyzed, including those who stop receiving treatment, according to the intent-to-treat principle [68]. Continuous outcome measures, including the primary outcome of reduction of days with cannabis abuse, will be analyzed using multivariate analysis of variance (ANOVA) mixed models with repeated measurements. This will include interaction analyses of time and type of treatment, in order to evaluate the effect over time. Binary outcome measures will be analyzed using multivariate logistic regression models. The subgroup of patients who complete the entire experimental treatment will be compared with all those randomized into the trial in order to determine risk factors for attrition. Sensitivity analyses will be carried out to evaluate the effect of treatment in patients that are inaccessible for follow-up. This will be conducted by multiple imputation methodology both using last observation carried forward, and assuming an increase in cannabis use among those lost to follow-up.

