## Discussion

The centralized randomization procedure offers strengths to the CapOpus trial by reducing the risk of selection and allocation bias [71,72]. The outcome assessments are blinded with the intent of being unbiased [71,72]. The planned intense follow up of patients coupled with intention-to-treat analyses should guard against attrition bias [71,72]. Also, the broad array of outcome estimates allows us to measure effects of treatment in many areas of life.

Apart from gathering evidence about best practice in treatment of cannabis abuse among young people with psychosis, the study will allow us to validate the TLFB measurement tool for cannabis against blood samples, something that to our knowledge has not been done previously.

Hopefully, the CapOpus intervention will carry positive effects. If this is so, this could substantially improve treatment of these patients. On the other hand negative consequences cannot be ruled out. The extra interventions in the experimental arm may potentially cause more patients to drop out from usual treatment. Should this occur, the addiction consultants in CapOpus will actively support the patients in resuming contact with the case managers.

Our trial may have several limitations. First, it is a rather small trial aiming at demonstrating a substantial intervention effect. In a sense, our trial may be viewed as a pilot for potentially larger trials at a later stage. Second, the large number of outcomes makes interpretation of significant findings difficult. Accordingly, our interpretation of significant findings at or close to the conventional level of p = 0.05 will be conservative. One further limitation of the trial is that there may be a crossover relating to the patients' case-managers. Due to the randomization procedure, the same case manager may have patients in both the experimental intervention and the control treatment arms. This spawns the risk that elements from the experimental intervention are incorporated into the treatment of patients in the control arm, potentially leading towards type II errors. It will be attempted to bypass this limitation by investigating outcome differences between control-group patients whose case managers also have patients in the CapOpus experimental intervention arm, and those whose case managers do not.

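### Therapy groups exist in the experimental arm only, but the sample size assumes independent patients and the described primary model names no group effect, so the standard error is too small if outcomes correlate within groups

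*Protocol article*

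**What the plan says.** The section on the CapOpus intervention describes a programme of one month of individual contact, three months of weekly 1½-hour group sessions alongside individual contact, and two further months of individual contact. On the groups it says: "The groups will consist of six to eight patients, with the addiction consultants as trainers". Group treatment is offered, and expected uptake is not stated.

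The section on the control treatment has it delivered by each patient's own case manager, with no trial therapy groups.

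The section on sample size and power starts from these inputs: "Truncating this to a more conservative 5 days, and assuming a standard deviation also of 5 days". It then says that "it becomes possible to calculate sample size for an independent samples t-test", and concludes: "with an α-level of 0.05 and a power of 0.90, the required number of patients in each intervention can be calculated to be 22". The only later adjustment is for 37% dropout, which gives at least 35 per arm. The recruitment aim is 60 to 70 per arm.

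The Statistics section says that continuous outcomes, the primary one included, "will be analyzed using multivariate analysis of variance (ANOVA) mixed models with repeated measurements", with interactions of time and treatment. It names no therapy-group or consultant effect.

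The Discussion notes that "the same case manager may have patients in both the experimental intervention and the control treatment arms". It treats this as possible contamination leading towards type II error and does not mention correlation within therapy groups.

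**The concern.** Patients in one therapy group share trainers, peers and a calendar period, so their outcomes may be more alike than those of patients in different groups. Because this happens in one arm only, the design is partially nested. A model for repeated measurements handles correlation between visits of the same patient. It does not handle correlation between different patients in the same group.

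If that correlation is positive and left out, the variance of the experimental-arm mean is understated. P-values for the primary comparison are then too small and confidence intervals too narrow. The minimum sample size, which rests explicitly on independence, is also somewhat optimistic.

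**Working it through.** **Inputs from the article.** Difference 5 days, SD 5 days, alpha 0.05, power 0.90, dropout 37%, groups of 6 to 8, and 60 to 70 recruited per arm. Sidedness is not stated. A two-sided test reproduces the stated 22, whereas a one-sided test would give 18.

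**Assumptions.** The ICC is not given and is taken as 0.01 to 0.10. Total SD is held at 5 in both arms. Analysed arms are of equal size. Controls are treated as unclustered.

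**Step 1: the plan's own figures.** n per arm = 2 × (1.960 + 1.282)² × (5/5)² = 21.01, rounded up to 22. The exact t-test power at 22 per arm is 0.8997. Allowing for dropout, 22/0.63 = 34.9, rounded up to 35. Both figures reproduce, so the arithmetic is right under independence.

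**Step 2: type I error.** The design effect in the experimental arm is DE = 1 + (m − 1) × ICC, where m is the number of analysed patients per group. The variance of the difference inflates by (1 + DE)/2. The real two-sided error of a nominal 5% test is 2 × [1 − Φ(1.96/√inflation)]. Full groups are taken as m = 7. With 37% lost, m = 7 × 0.63 = 4.4.

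| ICC | m = 7: DE, inflation, real error | m = 4.4: DE, inflation, real error |
|---|---|---|
| 0.01 | 1.06, 1.03, 5.3% | 1.03, 1.02, 5.2% |
| 0.02 | 1.12, 1.06, 5.7% | 1.07, 1.03, 5.4% |
| 0.05 | 1.30, 1.15, 6.8% | 1.17, 1.09, 6.0% |
| 0.10 | 1.60, 1.30, 8.6% | 1.34, 1.17, 7.0% |

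The true standard error exceeds the naive one by √inflation. At ICC 0.05 that is about 7% with m = 7 and 4% with m = 4.4. A simulation of a t-test that ignores groups (40,000 runs per setting, 64 to 66 per arm, groups of 6 or 8) gives 6.5% to 7.1% at ICC 0.05 and 7.8% to 9.4% at ICC 0.10, in line with the formula.

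**Step 3: minimum sample size.** n per arm = (1 + DE) × (1.960 + 1.282)² = (1 + DE) × 10.51, then divided by 0.63.

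- ICC 0.01, m = 6 to 8: 22 per arm, 35 after dropout (unchanged).
- ICC 0.05: m = 6 gives 2.25 × 10.51 = 23.6, so 24; m = 8 gives 2.35 × 10.51 = 24.7, so 25. After dropout, 39 to 40.
- ICC 0.10: m = 6 gives 2.50 × 10.51 = 26.3, so 27; m = 8 gives 2.70 × 10.51 = 28.4, so 29. After dropout, 43 to 47.

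**Step 4: power at the recruitment target.** With 37% lost, 60 to 70 recruited per arm leave 37 to 44 analysed. Power = Φ(√[n/(1 + DE)] − 1.96) for a 5-day difference. With the design effect of full groups of 6 to 8, this is 0.98 to 0.99 at ICC 0.05 and 0.96 to 0.99 at ICC 0.10.

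**The case against.** **The model may already contain a group term.** The Statistics section lists no random effects and does not say that repeated measurement is the only structure. The article is condensed, and an analysis plan that is not at hand may specify more. This stands: a reader might infer that the primary model is shown to treat patients as independent, but the text shows only that no group effect is named. Independence is explicit in the sample size section alone, and a later model term would not correct that calculation.

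**The ICC is unknown.** This also stands. The standard error is too small only if the ICC is positive, and at 0.01 nothing material changes.

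**Full groups of 7 are an upper case.** Group treatment is optional, lasts three of the six months, and runs beside individual contact. The final assessment comes four months after treatment ends. Dropout and non-uptake would dilute the correlation, which is why the figures for 4.4 members are shown. Consultants shared across groups could work the other way.

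**Case managers also cluster patients.** They serve both arms, so a shared case-manager effect partly cancels in the treatment difference, and ignoring it tends to make the naive standard error conservative. It could offset some of the group effect. A reader might take the Discussion's remark on case managers as a second source of inflated error, but the text does not support that. Nor does the possible offset remove the one-arm clustering that the design creates.

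**Findings near p = 0.05 will be read conservatively.** The Discussion promises this because of the many outcomes. It does not correct a standard error or an interval.

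**Conclusion.** The point holds conditionally. One-arm group delivery sits beside a sample size for independent patients and a primary model described without any group effect. If the within-group ICC is positive, the standard error is understated. For an assumed ICC of 0.02 to 0.10, the nominal 5% test runs at about 5.4% to 7.0% after dropout and 5.7% to 8.6% with full groups. The effect is negligible at 0.01 and worth correcting from about 0.05.

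The consequence is mainly type I error and interval width. A reader might infer that the trial is underpowered. At the bare minimum of 22 per arm and 7 per group, power by the normal approximation does fall, from 0.913 to 0.87 at ICC 0.05 and 0.83 at ICC 0.10. But that minimum is not the recruitment target, and at 60 to 70 per arm power for 5 days stays at about 0.96 or more up to ICC 0.10. The 22 and 35 are only mildly optimistic (24 to 25 and 39 to 40 at ICC 0.05).

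These figures rest on the assumed ICC, an SD of 5 in both arms, equal arms and no clustering among controls.

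**What to change.** - **Data.** Record each experimental patient's scheduled therapy group as groups form, whether or not the patient attends. Using the scheduled group respects intention-to-treat.
- **Model.** Add a group random effect in the experimental arm only. Treat controls, and experimental patients never scheduled to a group, as singletons. Groups form after baseline, so the effect must act on post-baseline visits, either as group-by-time or as a group intercept with the baseline value as covariate. A group intercept held constant over all visits would largely cancel from the time-by-treatment contrast and correct little.
- **Inference.** Use small-sample degrees of freedom. With 60/8 = 7.5 to 70/6 = 11.7, there will be only about 8 to 12 groups.
- **Sample size.** State an assumed ICC, for example 0.05, beside the minimum, which then reads 24 to 25 per arm, or 39 to 40 after dropout. The recruitment target can stay as it is.
- **Optional.** A sensitivity model with a case-manager effect. The comparison of controls by case-manager caseload planned in the Discussion already requires case-manager identity.

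The cost is one identifier, one more variance term and a slightly wider interval. The group variance will be imprecise with so few groups and may be estimated at zero.

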### Control treatment – treatment as usual

The control treatment consists of receiving the treatment that would have been available without participation in the trial, i.e. treatment as usual. The patient's case manager will carry out the control treatment. In essence, treatment as usual for cannabis abuse is part of the existing, manualized psychosocial and/or pharmaceutical treatment for psychotic illness; however, no explicit manual exists on ways in which cannabis abuse should be approached. Treatment as usual is thus not expected to be uniform. In particular, frequency of contacts may vary between case managers, and this will be registered and analyzed. However, the heterogeneous nature of the control treatment accurately reflects the current situation in Denmark, and we therefore consider this to be the appropriate treatment for analytical control.

Treatment as usual is carried out in one of three established facilities; the OPUS teams for early detection and treatment of young people with psychosis [35], the community mental health centers (CMHC) [36], and the assertive community treatment (ACT) teams [37]. The effect of treatment as usual on cannabis abuse in Denmark is unknown, but a randomized trial comparing OPUS treatment with other treatment (primarily CMHC) investigated prevalence of any comorbid diagnosis of harm or dependence syndrome at baseline and at one and two years follow-up. At baseline, 27% in both treatment arms had such a comorbidity, which decreased to 16 – 17% for OPUS patients and 21 – 22% for other patients [38].

